#### Phase III primary outcome measures

Incidence of PoSH at 6 months postsurgery—defined as the need for calcium and/or vitamin D supplements to treat symptoms or maintain adjusted calcium in the low normal range (between 2.1 and 2.3 mmol/L). This is in accordance with the national British Association of Endocrine and Thyroid Surgeons definition.^21^

#### Phase III key secondary outcome

Postoperative PTH over 6 months, measured at 1 day, 1 month and 6 months postsurgery.

#### Phase III secondary outcome measures

To compare NIRF+ICG and standard care in terms of:

Transient hypocalcaemia.Protracted hypoparathyroidism, defined as either an adjusted calcium of <2.1 mmol/L or the need for calcium and/or vitamin D supplements to treat symptoms or maintain adjusted calcium in the low normal range at 1 month post-surgery.Intra-operative complications graded using the ClassIntra classification.^22^Postoperative complications within 6 months of operation graded using the Clavien-Dindo classification.^23^Length of hospital stay in days post-surgery.Health related quality of life (HRQoL) at baseline, 1–6 months postoperation using the Short Form 36 Health Survey Questionnaire and Hypoparathyroid Patient Questionnaire instruments.Any episode of readmission to hospital within 6 months of operationHypercalcaemia occurring within 6 months of operation, defined as any adjusted calcium >2.6 mmol/L measured at 1 day, 1 month and 6 months post-surgery.

#### Phase III mechanistic outcome measures

To explore the effect of treatment-related decision-making on patient outcomes.

### Statistical considerations and analyses

#### Sample size

Bayesian optimisation^24 25^ was used to determine the combination of total sample size, phase II sample size and the decision boundaries for the test statistics at the phase II and phase III analyses (Z_II_ and Z_III_ in figures2  3) that minimise the expected sample size required while maintaining an overall significance level of 5% and overall power of at least 80%. Each design explored during the optimisation process was estimated empirically via simulations, using 1000 repeats, and the operating characteristics of this chosen optimal design were re-evaluated using 100 000 repeats. The chosen design has an overall type I error rate of 4.83% and achieves an overall power of 89.33%.

**Figure 2 F2:**
[figure not shown]
Operating characteristics of the proposed design under the null hypothesis.

**Figure 3 F3:**
[figure not shown]
Operating characteristics of the proposed design under the alternative hypothesis.

The target sample size is 454 patients (227 per treatment group), with an interim phase II analysis after 200 patients (100 per treatment group), to allow the trial to stop early due to futility. Assuming a 6-month PoSH rate of 10% in the control group, and 1-day hypocalcaemia rate of 25% and 12.5% in the control and the NIRF+ICG groups, respectively, this design yields around 89% power at the 5% level of significance to detect a relative reduction in 6-month PoSH of at least 70% (ie, a reduction to 3% 6-month PoSH in the NIRF+ICG group), allowing for a 10% drop-out rate. Additionally, this sample size estimate relies on the key assumption that patients who are not hypocalcaemic at 1 day postsurgery will not experience PoSH at 6 months.

#### Analysis methods

All analyses and patient populations will be predefined within the trial’s statistical analysis plan and reporting will be in line with Consolidated Standards of Reporting Trials guidelines. The primary phase II and phase III analyses will be conducted using the principles of intention-to-treat (ITT), meaning that participants will be analysed in the group to which they were randomised irrespective of whether or not they receive their allocated intervention. Patterns of missing data will be explored, and analyses appropriate to the suspected missing data mechanism will be conducted, where necessary.

#### Interim analysis (phase II analysis)

Only the phase II primary endpoint will be assessed at the phase II analysis.

The phase II analysis will compare the 1-day hypocalcaemia rates between the arms using multilevel logistic regression, incorporating random effects with respect to surgeon and adjusting for the minimisation factors. At the phase II analysis, the trial will continue only if there is sufficient evidence of superiority of the experimental treatment compared with the control. This will be determined via a one-sided critical region for Z_II_, the Z-value from the multilevel logistic regression model’s Wald test of the adjusted log-odds ratio of 1-day hypocalcaemia. If Z_II_<−0.84162, then the trial will continue; otherwise, it will stop for futility. This decision boundary is equivalent to testing using a one-sided 20% significance level at the phase II analysis. The trial is designed based on a binding stop/go decision.

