### Trial setting and recruitment

Participants will be recruited from approximately 10 research sites in the UK over a 32-month period. A phase II interim analysis will be performed after adequate phase II primary endpoint data (transient hypocalcaemia on the day after surgery) has been collected, approximately 1 month after randomising 200 participants.

Patients requiring total or completion thyroidectomy will be identified prior to elective surgical admission. Suitability for trial inclusion will be assessed according to the eligibility criteria in table 1, and potential participants will be approached in the surgical clinic.

**Table 1 T1:** NIFTy patient eligibility criteria

Inclusion criteria	Exclusion criteria
Aged ≥18 years. Able to provide written informed consent. Due to undergo total or completion thyroidectomy with or without central neck dissection (indications for surgery may include Graves’ disease, suspected or confirmed thyroid cancer and goitre with compressive effects). ASA (American Society of Anesthesiologists) </= 3. Able and willing to comply with the terms of the protocol including participant completed questionnaires.	Patients undergoing concomitant parathyroid or thoracic surgery. Patients undergoing reoperative thyroid surgery (except completion thyroidectomy after previous contralateral lobectomy). Documented hypo or hypercalcaemia within the last 3 months prior to planned date of thyroid surgery, defined as adjusted calcium <2.1 mmol/L or >2.6 mmol/L. Pregnancy. Known allergy to ICG, iodine or iodine dyes. Patients with significant renal impairment (defined as eGFR <40 mL/min/1.73 m^2^ (or a serum creatinine value >10% of upper value for normal institutional limits if eGFR is not performed locally). Taken calcium or active vitamin D supplements (such as alfacalcidol or calcitrol) in the 2 weeks prior to randomisation or due to receive prophylactic treatment with calcium and/or active vitamin D supplements perioperatively.

eGFRestimated glomerular filtration rateICGindocyanine green

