### Randomisation and blinding

Following confirmation of written informed consent and eligibility, participants will be randomised into the trial. Randomisation will be performed centrally using the central automated 24-hour randomisation system. Participants will be randomised on a 1:1 basis to receive thyroid surgery performed either as per standard care or with NIRF+ICG and allocated a unique trial number. A computer-generated minimisation programme that incorporates a random element will be used to ensure treatment groups are well-balanced for the following participant characteristics: operating surgeon, indication (Graves’ disease, cancer, etc) and sex. Clinical assessments and baseline questionnaires will be completed before randomisation. Treatment allocation will not be blinded to participants, medical staff or clinical trial staff.

The timing of clinical assessments and data collections points are summarised in table 2.

**Table 2 T2:** Clinical assessments and data collection timepoints

Events	Baseline/preop	Surgery	1 day post-op	1 month post-op	6 months post-op
Clinical assessments/investigations					
Clinical examination	**✓**		**✓**	**✓**	**✓**
Biochemistry	**✓**		**✓**	**✓**	**✓**
Trial consent	**✓**				
Operative details		**✓**			
Complications		**✓**		**✓**	**✓**
Data collection time points					
Eligibility eCRF	**✓**				
Randomisation eCRF	**✓**				
Baseline eCRF	**✓**				
Operative eCRF		**✓**			
1 day after surgery f/up eCRF			**✓**		
1 month after surgery f/up eCRF				**✓**	
6 months after surgery f/up eCRF					**✓**
HRQoL					
SF-36	**✓**			**✓**	**✓**
HPQ-28	**✓**			**✓**	**✓**

eCRFelectronic case report formHPQ-28Hypoparathyroid Patient QuestionnaireHRQoLhealth related quality of lifeSF36Short Form 36 Health Survey Questionnaire

Preoperative investigations and preparation will be as per institutional protocol. A biochemical assessment will be carried out including thyroid function, renal function, calcium, PTH, vitamin D, magnesium, phosphate, and urea and electrolytes, details of which will be recorded on the trial case report forms (CRFs). Participants must not be given prophylactic treatment with calcium and/or active vitamin D supplements perioperatively. However, any vitamin D deficiency that is detected during investigation may be treated as per local protocols.

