### Outcome measures

#### Phase II primary outcome measure

Transient hypocalcaemia, defined as any adjusted calcium of <2.1 mmol/L at 1 day postsurgery.^20^

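### The phase II gate model is valid but omits pre-operative calcium, forgoing a small and nearly free gain in power at a binding decision

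*Protocol article*

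**What the plan says.** All references are to the protocol article.

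- **Model.** The section on the interim (phase II) analysis compares day-1 hypocalcaemia between arms by "multilevel logistic regression, incorporating random effects with respect to surgeon and adjusting for the minimisation factors". Z_II is the Wald Z for the adjusted log-odds ratio from that model, and the trial continues only if Z_II < −0.84162.
- **Status of the boundary.** The boundary amounts to a one-sided 20% test, and the same section makes a stop mandatory: "The trial is designed based on a binding stop/go decision".
- **Adjustment set.** Under Randomisation and blinding, minimisation keeps the groups "well-balanced for the following participant characteristics: operating surgeon, indication" and sex. No calcium variable is among the factors.
- **Outcome.** "Transient hypocalcaemia, defined as any adjusted calcium of <2.1 mmol/L at 1 day postsurgery".
- **Baseline data.** Under Randomisation and blinding: "A biochemical assessment will be carried out including thyroid function, renal function, calcium, PTH, vitamin D, magnesium, phosphate, and urea and electrolytes". The results go on the CRFs, and Table 2 ticks biochemistry at baseline.
- **Eligibility.** Table 1 excludes documented hypo- or hypercalcaemia in the 3 months before planned surgery, "defined as adjusted calcium <2.1 mmol/L or >2.6 mmol/L".

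**The concern.** The gate outcome is a cut of blood calcium one day after surgery. The pre-operative value of the same analyte is an obvious candidate predictor, and the plan already provides for collecting it. Leaving it out of a logistic model loses some power if the two values are correlated.

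The gate is where that loss would count. It rests on few events, about 100 × 0.25 + 100 × 0.125 = 37.5 under the design assumptions, and a stop is binding. It is also where most of the lost power goes: of the roughly 10.5 points by which simulated overall power falls short of 100%, about 7 come from stopping wrongly at the gate.

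This is not a matter left to the statistical analysis plan. The protocol names the adjustment set and defines the boundary on the Z from that model.

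**Working it through.** **Inputs from the protocol.** 100 per arm at the gate and 227 per arm in total; day-1 hypocalcaemia 25% versus 12.5%; 6-month PoSH 10% versus 3%, occurring only in patients hypocalcaemic on day 1; 10% drop-out; boundaries Z_II < −0.84162 and |Z_III| > 1.28155.

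**Step 1: reproduce the stated figures without the covariate.**

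Gate power from the two-proportion formula:
- pooled rate (0.25 + 0.125)/2 = 0.1875
- null SE = √(2 × 0.1875 × 0.8125/100) = 0.0552
- alternative SE = √(0.25 × 0.75/100 + 0.125 × 0.875/100) = 0.0545
- power = Φ[(0.125 − 0.84162 × 0.0552)/0.0545] = Φ(1.44) = 92.5%

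A two-stage simulation with Wald log-odds-ratio tests (400,000 repeats, drop-out at 6 months only) gives:

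| Quantity | Simulated | Stated |
|---|---|---|
| Gate pass, design effect | 92.9% | not given |
| Overall power | 89.5% | 89.33% |
| Overall type I error | 4.79% | 4.83% |

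The stated operating characteristics are therefore reached with no baseline covariate. Wrong stops are 100 − 92.9 = 7.1 points of a total loss of 100 − 89.5 = 10.5 points, about two thirds.

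**Step 2: add baseline calcium to the gate model.** Baseline and day-1 calcium are taken as bivariate normal with correlation r, and day-1 calcium is cut to give the stated rates. The logistic model is fitted with and without baseline calcium, and the share of trials with Z_II < −0.84162 is counted. The protocol gives no value for r, so a range is shown. The weaker effect (25% versus 17.5%) is illustrative and not a design assumption. Overall power leaves the phase III test unadjusted and uses 10% drop-out at 6 months. Each cell reads without → with.

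| r (assumed) | Gate pass, 25% v 12.5% | Gate pass, 25% v 17.5% | Gate pass, null | Overall power |
|---|---|---|---|---|
| 0 | 92.8 → 92.7% | 67.7 → 67.3% | 19.9 → 20.2% | 89.1 → 89.0% |
| 0.3 | 92.7 → 93.4% | 68.4 → 68.8% | 19.7 → 19.8% | 89.2 → 89.7% |
| 0.5 | 92.9 → 94.8% | 68.6 → 71.4% | 19.6 → 20.2% | 89.4 → 90.9% |
| 0.6 | 92.8 → 95.6% | 68.2 → 73.1% | 19.4 → 20.2% | 89.6 → 92.0% |
| 0.7 | 93.0 → 96.8% | 68.0 → 75.6% | 19.1 → 19.4% | not run |

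The columns come from separate runs of at least 20,000 repeats. The simulation standard error is about 0.2 points for the design-effect gate pass (√(0.93 × 0.07/20,000) = 0.18 points) and about 0.3 points for the weaker effect and the null. The figures without the covariate should not depend on r, and their drift down a column is simulation noise. Other runs at r = 0.3 put the gate gain at 0.3 to 0.5 points, so about half a point is a fair summary there. Overall type I error was 4.5 to 4.7% with or without the covariate.

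**Limits of the check.** These models contain treatment, with or without baseline calcium. They omit the surgeon, indication and sex terms of the planned model, so the increment over that model has not been estimated.

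**The case against.** The strongest case against raising this is that nothing in the plan is wrong. Adjusting for the factors used in allocation is standard, the test holds its one-sided 20% level, and a design required to reach 80% power reports 89.33% with the risk of a wrong stop already counted. All of that stands. A reader might infer from the omission that the gate is biased, invalid or underpowered; the protocol's own figures, reproduced above, do not support that.

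Other parts of the objection also stand:

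- **The gain rests on an unknown correlation.** It becomes worth discussing only at r of about 0.5 or more. The 2.1 to 2.6 mmol/L eligibility window narrows the baseline range and may lower r.
- **Gate pass overstates the benefit.** The trial needs to pass the gate and then succeed in phase III, and overall power gains less. At higher r, part of the gain may reflect a slightly higher pass rate under the null.
- **Complete baseline data cannot be assumed.** A reader might take it that adjusted calcium is measured in every patient. The text plans the assessment for every patient but leaves pre-operative investigations to institutional protocol. It lists calcium there, and adjusted calcium only in the eligibility criterion. Completeness is unknown, so a rule for missing values is needed.

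What the objection does not remove is the balance of cost and benefit. At r = 0 the covariate changes the pass probability by no more than simulation error; at moderate r it lowers the risk of an irreversible wrong stop.

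**Conclusion.** The planned gate is valid and the design delivers its stated power. Leaving pre-operative calcium out of the phase II model gives up a small gain in efficiency; it is not an error in the plan. At the design effect, the probability of continuing rises by about 0, 0.5, 2 and 3 points for r = 0, 0.3, 0.5 and 0.6, and overall power by about 0, 0.5, 1.5 and 2.4 points. At r = 0.5, wrong stops fall from about 7% to about 5%. The gain at the gate is larger if the true effect is smaller than planned and r is moderate or high. The pass rate under the null stays near 20%.

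These sizes depend on the assumed r, on a bivariate-normal model, and on simulations without the surgeon, indication and sex terms. Severity is low and the change is optional.

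**What to change.** Before any interim data are seen:

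- Prespecify pre-operative adjusted calcium as a continuous fixed covariate in the phase II model, alongside the random surgeon effect and the minimisation factors.
- Use the same covariate in the phase III secondary analysis of transient hypocalcaemia.
- State that the adjusted value is the one used, and give a simple rule for missing baseline values, for example imputing the mean.
- Keep the −0.84162 boundary and re-run the design simulations with the full model over a range of r, to confirm the gate level, overall type I error and power.

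The cost is one model term, one missing-data rule and a repeat of the simulations. The sample size is unchanged and no new assessment is needed beyond the planned baseline biochemistry.

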#### Final analyses (phase III analyses)

The primary phase III analysis will compare 6-month PoSH rates between the arms using multilevel logistic regression incorporating random effects with respect to the surgeon and adjusting for the minimisation factors. At the phase III analysis, evidence of a difference between the treatment groups will be determined via a two-sided critical region for Z_III_, the Z-value from the multilevel logistic regression model’s Wald test of the adjusted log-odds ratio of the 6-month PoSH. If |Z_III_|>1.28155, then the trial will conclude that there is a significant difference between the treatment arms. This decision boundary is equivalent to testing using a two-sided 20% significance level.

Secondary endpoints with binary measures will be analysed using multilevel logistic regression adjusting for the minimisation factors, incorporating random effects with respect to surgeon. Secondary endpoints with continuous measures will be analysed using multilevel generalised linear models incorporating random effects with respect to surgeon and assuming normal errors at the patient level. If the assumption of normal errors is clearly violated by the observed response data, then transformations of the response variable as well as alternative distributional assumptions will be explored, and the choice of a transformation and/or alternative distribution will be driven by comparative measures of model fit. Models for endpoints that are measured at multiple time points will also include an additional level to account for repeated measures, so that longitudinal effects can be assessed.

The mechanism of the NIRF+ICG intervention and how treatment-related decision-making is affected will be investigated using exploratory methods looking at the effects of the key surgical components identified in the embedded process evaluation.

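### The phase III decision rests on a Wald Z, which goes to about 0 if the NIRF+ICG arm has no PoSH events; a likelihood-ratio statistic or a named fallback would close this low-probability gap

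*Protocol article*

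**What the plan says.** Under Final analyses (phase III analyses), the protocol article compares 6-month PoSH between arms by multilevel logistic regression, with surgeon as a random effect and adjustment for the minimisation factors. The decision statistic Z_III is the Z-value from the "Wald test of the adjusted log-odds ratio of the 6-month PoSH", and a significant difference is concluded if |Z_III| > 1.28155.

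The Sample size section gives the expected event counts. It is worded as "Assuming a 6-month PoSH rate of 10% in the control group", the alternative is "a reduction to 3% 6-month PoSH in the NIRF+ICG group", and the calculation is described as "allowing for a 10% drop-out rate" with 227 patients per arm. The design is intended "to detect a relative reduction in 6-month PoSH of at least 70" per cent, so 3% is the highest NIRF+ICG rate within the target and lower rates are also in scope. The same section states an overall type I error of 4.83% and power of 89.33%, and sets 80% as the minimum power.

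The article gives no other statistic for an arm without events. Analysis methods defers the predefinition of all analyses to the SAP, which is not shown.

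**The concern.** With about 6 events expected in the NIRF+ICG arm, the count could be very low if the technique works better than assumed. The Wald Z divides the estimated log-odds ratio by its standard error. When an arm has no events the estimate has no finite maximum. As the fit iterates, the standard error grows much faster than the estimate, and the ratio tends to 0. A rule tied to this ratio can therefore fail at the most favourable result the trial could produce.

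The trial is also unblinded. Choosing another statistic after an empty arm has been seen would be a data-driven change to the primary test.

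**Working it through.** **Inputs (Sample size section).** 227 per arm with 10% drop-out: 227 × 0.9 ≈ 204 analysed per arm. Control events: 0.10 × 204 ≈ 20. NIRF+ICG events: 0.03 × 204 ≈ 6.

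**Step 1: the plan's own figures.** I simulated the two-stage design with unadjusted 2×2 Wald statistics, 1,000,000 repeats, the stated boundaries and day-1 hypocalcaemia of 25% and 12.5%. PoSH was confined to patients hypocalcaemic at day 1, as the protocol assumes. Drop-out was applied to the 6-month endpoint only, and an empty arm counted as Z = 0. Power is 89.3% (stated 89.33%) and type I error 4.86% (stated 4.83%). The stated figures reproduce with the empty-arm failure already included.

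**Step 2: the statistic at low counts.** With a = 20 control events, b NIRF+ICG events and n = 204 per arm:

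- Wald Z = [ln(b/(n−b)) − ln(a/(n−a))] / √(1/a + 1/(n−a) + 1/b + 1/(n−b)).
- Signed-root LR = −√(2 × [log-likelihood with separate rates − log-likelihood with a common rate]).

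Example, b = 1: the numerator is ln(1/203) − ln(20/184) = −5.313 + 2.219 = −3.094. The standard error is √(1 + 1/203 + 1/20 + 1/184) = 1.030. Z = −3.00.

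| NIRF+ICG events (vs 20) | Wald Z | Signed-root LR Z |
|---|---|---|
| 6 | −2.68 | −2.91 |
| 3 | −3.16 | −3.85 |
| 2 | −3.20 | −4.23 |
| 1 | −3.00 | −4.69 |
| 0 | about 0 | −5.36 |

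For b = 0 the LR is 2 × [20 ln 2 + 184 ln(184/204) − 388 ln(388/408)] = 2 × 14.38 = 28.76, whose root is 5.36.

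**Step 3: 20 vs 0 in fitted models.** Plain maximum likelihood after 25 iterations gives a log-odds ratio of about −24, a standard error of about 34,000 and Z = −0.0007. A covariate-adjusted logistic fit gives −0.002. A random-intercept fit gives about −0.03, using dummy covariates and 20 assumed surgeons. None passes 1.28155. On the same data the score Z is −4.59, the penalised (Firth-type) Wald Z is −2.66 and Fisher's p is 1.2 × 10⁻⁶; all of these pass. A fit stopped after 5 iterations gives Z = −2.53 and would pass, so the outcome could depend on a software setting.

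**Step 4: how often an arm is empty.** P(0 events) = (1 − p)^204.

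- p = 3% (70% reduction): 0.97^204 = 0.2%
- p = 2% (80% reduction): 0.98^204 = 1.6%
- p = 1% (90% reduction): 0.99^204 = 12.9%

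**Step 5: effect on power and type I error.** A second unadjusted two-stage simulation, with the same boundaries, compared the two phase III statistics:

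| True NIRF+ICG rate | Power, Wald rule | Power, LR statistic |
|---|---|---|
| 3% | 89.1% | 89.3% |
| 2% | 90.6% | 92.2% |
| 1% | 80.7% | 92.9% |

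Global-null type I error was 4.67% with either statistic. If drop-out is applied at both stages, literal-rule power at 1% is 78.9%, against 90.9% when an empty arm counts as significant. About 80% is therefore a fair summary at that rate.

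**The case against.** The strongest reply has four parts.

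- **Separation and non-convergence are ordinary SAP content.** The article defers to an SAP that is not shown, and a Wald test in logistic regression is a standard choice. It stands that the missing fallback is not in itself an error and that the SAP may already supply one. But the article does more than stay silent: it names the statistic and gives a five-decimal boundary, and an SAP that follows it inherits the behaviour.
- **The trigger is rare.** At the design rate it is 0.2%. A material loss needs a true rate near 1%, which with 12.5% day-1 hypocalcaemia means 1/12.5 = 8% of hypocalcaemic NIRF+ICG patients going on to PoSH, against 10/25 = 40% in control. The Discussion says an effect on long-term PoSH has not been convincingly shown. This stands and sets the weight of the point. The target of 70% or more includes such rates but does not predict them.
- **Low but non-zero counts do no harm here.** A reader might infer from the table that the Wald Z misleads at every low count. It is smaller than the likelihood-ratio Z throughout, but with 1, 2, 3 or 6 events against 20 it remains more than twice 1.28155.
- **The protocol nowhere says it would declare no difference.** A reader might infer that from the rule. The text states only when a significant difference is concluded and does not say how a separated fit would be read. The supported statement is that the rule, applied literally with unpenalised maximum likelihood run to convergence, could not conclude a difference.

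**Conclusion.** The point holds as a robustness improvement of low probability. An empty NIRF+ICG arm would leave the named statistic unable to cross its boundary, whatever the control count. At the design alternative this costs about 0.2 percentage points of power. At a true rate of 2% it costs about 1.6 points (90.6% against 92.2%), and at 1% about 12 points (80.7% against 92.9%).

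A reader might infer that the stated 89.33% power or 4.83% type I error is wrong. The documents do not support that: both reproduce with empty arms counted as failures. Nor does the point extend to phase II, where the chance of no day-1 hypocalcaemia among 100 NIRF+ICG patients at 12.5% is 0.875^100, about 2 in a million.

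The figures assume 204 analysed per arm, the protocol's event rates and link between the two endpoints, unadjusted statistics in the simulations, and ordinary maximum likelihood without penalisation.

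**What to change.** Define Z_III as the signed square root of the likelihood-ratio statistic for the treatment effect from the same multilevel logistic model, and keep |Z_III| > 1.28155. At minimum, keep the Wald Z but name in advance the likelihood-ratio or penalised statistic that replaces it if an arm has no PoSH events. Z_II can stay as it is.

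The cost is one sentence in the protocol or SAP and one extra model fit. Unadjusted simulation shows no type I error penalty (4.67% with either statistic). Because the boundaries were chosen by simulation, the sponsor should confirm this in its own simulation of the design before fixing the wording. If the SAP already contains such a fallback, a cross-reference is enough.
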